#### Exploratory Endpoint Analysis

Data on abstinence (binary—yes and no) will be evaluated at 9 saliva drug screen and timeline followback time points at weeks 1-8 and week 12. The association between abstinence and engagement will be evaluated using a generalized estimating equation model. A given week will be considered negative if a participant has no indication of opioid use on the saliva drug screens or timeline followback. Missing data will be ignored if saliva drug screens or a timeline followback is available for a given time point. In the case where saliva drug screens and timeline followback methods yield data that do not agree, the week will be considered positive.

The relationship between engagement and retention will be assessed using a Cox proportional hazards model with time to dropout as the dependent variable and the number of active sessions as an independent variable. This analysis will be performed separately for each treatment arm.

Patient assessment of skill acquisition (Cognitive Behavioral Therapy Skills Questionnaire) will be evaluated with repeated measures mixed model analysis consistent with the primary endpoint. Results will be presented for the total Cognitive Behavioral Therapy Skills Questionnaire score, the Behavioral Activation Score, and the Cognitive Restructuring score.

Medication adherence will be evaluated using saliva drug screens and, when possible, confirmed by urine drug screen (positive result for buprenorphine and norbuprenorphine). Differences between the treatment arms in medication adherence will be assessed with a generalized estimating equation analysis consistent with the abstinence analysis.

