### Study Procedures

#### Overview

All study visits will be conducted remotely. Each prospective participant will complete a short screening assessment, and if basic eligibility is confirmed, complete informed consent procedures and sign an electronic informed consent form prior to completing the baseline assessment. After baseline assessments, participants will be randomly assigned to either reSET-O or PEAR-008 groups. Study staff will assist each participant with installation of their assigned digital therapeutic on their mobile device. Staff will provide training on the app’s use. Study participants will be enrolled for 12 weeks, with weekly virtual sessions during weeks 1-8 and a final visit at week 12, to evaluate the impact of reSET-O and PEAR-008 on participant engagement and treatment outcomes. Participants will also complete slightly longer assessments at weeks 4 and 8.

Weekly study assessments completed during the first 8 weeks of treatment include saliva drug screening (participants will receive drug screening equipment on a regular basis by mail; urine drug screen results may be retrieved from the electronic medical record for AREF participants), timeline followback [29], and adverse event reporting. Additional self-report assessments will be delivered at week 4 and week 8.

Participants will attend a virtual end of treatment study session at 12 weeks to complete the following: saliva drug screening, timeline followback, and adverse event reporting assessment. Additional measures will be assessed at the 12-week follow-up visit (Table 1).

**Table 1 table1:** Study objectives and endpoints.

Objective			Endpoint

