**Exploratory**			
	To evaluate the association between engagement with PEAR-008 compared to reSET-O and treatment outcomes (abstinence and retention)	Daily and weekly use patterns; saliva (or urine drug screen for AREF^a^ participants only) and self-report; time to dropout	
	To evaluate skills acquisition at week 4 and week 8 of PEAR-008 compared to reSET-O	Cognitive Behavioral Therapy Skills Questionnaire	
	To evaluate medication adherence of PEAR-008 compared to reSET-O	Saliva drug screen (or urine drug screen, for AREF participants only)	

^a^AREF: Addiction Research and Education Foundation.

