### Endpoints

#### Primary Endpoint Analysis

Engagement with PEAR-008 and reSET-O will be defined as the number of active sessions per week. A session is defined as a set of in-app events with the same session ID. An active session is any session that contains some active participation in the app such as navigating to a different screen, engaging with a learning module, or responding to a notification. This endpoint was selected to allow a 1:1 comparison of content delivery method (eg, brief chapters vs longer lessons). The number of active sessions per week will be evaluated with a repeated measures mixed model of the form: *Number of Sessions in a Week = Week + Treatment + Week × Treatment + Subject Error + Random Error*. To evaluate the impact of treatment, this repeated measures mixed model will be compared to another of the form: *Number of Sessions in a Week = Week + Subject Error + Random Error* with a likelihood ratio test. The likelihood ratio test will be evaluated using model fit to maximize the log-likelihood.

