#### Secondary Endpoint Analysis

Abstinence will be self-reported by patients via timeline followback and assessed as the absence of opioids (except buprenorphine) on saliva drug screens. Data on abstinence (binary yes and no) will be evaluated with the 9 possible saliva drug screens and urine drug screen and timeline followback data at weeks 1-8 and week 12. Differences between the treatment arms in abstinence will be assessed with a generalized estimating equation analysis using the binomial abstinence outcome as the dependent variable, assessment time, treatment, and the interaction between assessment time and treatment as fixed effects and subject as a random factor. This generalized estimating equation will be compared to a second generalized estimating equation without a treatment term using a likelihood ratio test to evaluate the impact of treatment. A treatment responder analysis will also be conducted, with a treatment responder defined as someone with ≥80% of all saliva drug screens and urine drug screens and timeline followback reports negative for all nonprescribed opioids over the course of the trial.

Treatment retention will be measured as time to dropout (number of days from baseline to last face to face contact) and analyzed using the Kaplan Meier method followed by a log rank test to compare treatment groups.

Patient assessments of recovery capital (Brief Assessment of Recovery Capital–10) resilience (Connor-Davidson Resilience Scale–10) and severity of co-occurring psychiatric symptoms (Patient Health Questionnaire–8 and Generalized Anxiety Disorder Questionnaire–7) will be evaluated with a repeated measures mixed model in a manner consistent with the primary endpoint.

Participants’ use patterns with PEAR-008 and reSET-O will include total time engaged, number of lessons and chapters completed, number of lessons and chapters repeated, number of completed self-report assessments, and response to notifications. Descriptive statistics of each treatment arm will be summarized and differences between PEAR-008 and reSET-O will be assessed with a *t* test (or its nonparametric alternative if the distributional assumptions are violated).

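### The Cox model for engagement and retention leaves the time form of its session count open; read as a count over follow-up it is biased towards a protective association

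*Protocol article*

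**What the plan says.** The Exploratory Endpoint Analysis section of the protocol article relates engagement to retention through a "Cox proportional hazards model with time to dropout as the dependent variable and the number of active sessions as an independent variable". It adds: "This analysis will be performed separately for each treatment arm". It gives no time window for the count, no time-dependent form and no scaling to time at risk.

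Four other places bear on how the sentence is read:
- **Outcome.** Secondary Endpoint Analysis defines retention as "time to dropout (number of days from baseline to last face to face contact").
- **Session.** Primary Endpoint Analysis states: "An active session is any session that contains some active participation in the app". This is a count that grows with follow-up.
- **Engagement.** The same section states: "Engagement with PEAR-008 and reSET-O will be defined as the number of active sessions per week". The Cox sentence does not repeat the weekly scaling.
- **Objective.** Table 1 words the exploratory aim as "To evaluate the association between engagement with PEAR-008 compared to reSET-O and treatment outcomes (abstinence and retention"). Its endpoint cell begins "Daily and weekly use patterns; saliva (or urine drug screen for AREF" and gives no covariate form.

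Follow-up is described in the Study Procedures overview: "Study participants will be enrolled for 12 weeks, with weekly virtual sessions during weeks 1-8 and a final visit at week 12".

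**The concern.** A Cox model compares, at each dropout time, the covariate of the person who leaves with the covariates of those still at risk. If the covariate is each person's count over the whole of follow-up, the model uses at day 0 information that only arises later. A low count is then partly a consequence of leaving early, so a protective hazard ratio can arise when engagement has no effect. This is the bias of a future-dependent covariate, often called immortal-time bias.

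This is the only analysis in the article that links app use to retention, and the Introduction calls engagement critical to keeping patients in treatment. An artefact in the protective direction would look like confirmation of that rationale.

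**Working it through.** **The plan's own figures.** The article gives no figure for this analysis. Its only sizing figure is 130 participants for d=0.50, α=.05 and power 0.80. At 1:1 that is 130/2 = 65 per arm, and a two-sided t test then has power 0.808, so the stated figure reproduces. The 65 per arm is carried forward because the Cox model is fitted by arm.

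**Mechanism in two participants.** Assume that both use the app 5 times a week while in the study. One is last seen at week 2 and the other completes week 12.

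| Covariate | Leaves at week 2 | Completes week 12 |
|---|---|---|
| Total, constant use | 5×2 = 10 | 5×12 = 60 |
| Mean per week in study, constant use | 10/2 = 5 | 60/12 = 5 |
| Mean over 12 weeks, zeros after dropout | 10/12 = 0.83 | 60/12 = 5 |
| Mean per week in study, use falling as 5·exp(−0.1t) | 50(1−e^−0.2)/2 = 4.53 | 50(1−e^−1.2)/12 = 2.91 |

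Two equally engaged people differ sixfold on the total. Averaging over a fixed 12 weeks only rescales the total. Averaging over time in study removes the artefact under constant use. Under declining use it makes the early leaver look more engaged.

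**Null simulation.** Each participant's session rate was drawn independently of dropout time, so the true hazard ratio is 1. There were 65 participants per arm, 84 days of follow-up, 300 replicates per scenario (at least 290 usable) and a likelihood ratio test at 5%. The Monte Carlo standard error at 5% is √(0.05×0.95/300) = 1.3 percentage points.

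Assumptions not in the article: dropout 15-50%; mean 2 or 5 sessions per week; gamma shape 1 or 3 between participants; decline in use of 0, 0.1 or 0.2 per week; use after dropout of 0, 50% or 100% of the earlier rate.

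| Covariate and scenario | Rejection at nominal 5% |
|---|---|
| Total; constant use; 15% dropout | 59-83% |
| Total; constant use; 30% dropout | 81-97% |
| Total; constant use; 50% dropout | 94-100% |
| Total; declining use; 30% dropout | 38-91% |
| Total; 30% dropout; half of use continues after dropout | 24% |
| Total; 30% dropout; all use continues | 5% |
| Mean weekly rate in study; constant use, stopping at dropout | 5-9% |
| Mean weekly rate in study; declining use | 21-56% |
| Previous-week sessions, time-dependent | 4-7% |
| Week-1 sessions, day-7 landmark | 4-8% |

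Where use stops at dropout, essentially every rejection for the total is protective, with median hazard ratios of 0.61-0.85 per 10 sessions. For the mean weekly rate under declining use, nearly every rejection is in the harmful direction. The previous-week and landmark forms have median hazard ratios between 0.98 and 1.02.

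A second set of null simulations, also with 65 per arm, agrees. The total rejected in 62-98% with use stopping at dropout (median hazard ratio 0.49-0.84 per 10 sessions), 44% if half of use continued and about 4% if all continued. The mean weekly rate rejected in 74% under declining use. A week-4 landmark rejected in 3-6%.

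**The case against.** **The text may mean sessions per week.** The sentence says neither total nor fixed, and both the definition of engagement and Table 1 point to weekly use. Coding a covariate over time is also often left to an analysis plan, which is not shown. It is fair that the article does not commit to the total. But the weekly reading does not make the analysis safe. A mean over time in study is biased the other way when use declines, and a mean over 12 weeks with zeros after dropout is equivalent to the total. Only a time-updated or early-window covariate avoids both, and the sentence states neither.

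**App use may outlast study contact.** Dropout is the last contact with the participant, whereas sessions are logged by the app and stored in the cloud. Nothing says that logging ends at last contact. This objection stands as a limit on size: the artefact weakens if use continues and disappears if it continues in full. The article does not say which will happen.

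**Separate fits by arm are defensible.** The two apps generate sessions differently: PEAR-008 requires a daily check-in and rewards daily use, while reSET-O prompts for reports every 72 hours. A reader might infer from the wording of Table 1 that fitting by arm is an error. The documents do not support that, because the aim is exploratory and promises no between-arm test. What remains is that two separate hazard ratios do not by themselves compare the association between arms.

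**Conclusion.** The point holds as a bias in an exploratory analysis whose covariate is not tied to time. Under the count reading, and with use stopping at dropout, roughly 40-100% of null analyses would be nominally significant, almost always in the protective direction. Under the mean-rate reading, the result is about nominal with constant use and biased in the harmful direction with declining use. All of these sizes rest on assumed dropout and usage, because the article gives neither.

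A reader might go further and infer that the model is certain, or nearly so, to show that engagement prevents dropout. The documents do not support that. The covariate form is open, the rejection rate depends on the assumed inputs, and it falls to 24-44% if half of use continues after last contact and to about 5% if all does. The article also speaks of a relationship and an association, not of prevention.

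The primary endpoint, the sample size and the randomised retention comparison (Kaplan-Meier and log rank) are unaffected.

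**What to change.** State the covariate's time form in the Exploratory Endpoint Analysis section, by one of two routes:
1. **Time-dependent.** Enter active sessions in the previous week, updated weekly, with risk time starting once the first week is complete.
2. **Landmark.** For example, use sessions in weeks 1-4 to predict dropout after week 4 among those still in the study.

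Describe the result as an association. People about to leave may already be using the app less, and neither route removes that.

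To address the comparison worded in Table 1, add one model with treatment, engagement and their interaction, and keep the arm-specific hazard ratios. State that the interaction test will have low power. At an assumed 30% dropout there are 65×0.30 = 19.5, or about 20, dropouts per arm, and with equal precision the standard error of the difference in log hazard ratios is √2 times that of either arm.

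The cost is wording and restructuring of app logs already collected. The landmark's downside is that it excludes earlier dropouts. With a constant hazard and 30% dropout by week 12, the share gone by week 4 is 1−0.70^(4/12) = 11%, or about 7 of the 20 per arm. The time-dependent form loses only those who leave in the first week.

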### Study Population and Sample Size

The trial will include 130 adults aged 18 to 60 years with opioid use disorder who are already receiving buprenorphine treatment, with no criteria regarding gender identity, race, or ethnicity.

Inclusion criteria are having the ability to provide informed consent, age 18 to 60 years, having adequate English proficiency, being within the first 120 days of starting buprenorphine, receiving buprenorphine pharmacotherapy under the care of a licensed health care provider and being willing to provide the name of the provider or practice, being capable of using common software apps on a smartphone, and having access to an internet-enabled smartphone that meets minimal operating system requirements for the duration of the study. Exclusion criteria are having a history of reSET-O use, having participated in user-testing of PEAR-008 or any investigational drug trials within 30 days of trial enrollment, or currently receiving methadone or naltrexone pharmacotherapy.

The sample size and power were based on the primary engagement outcome, determined by frequency of interaction with the intervention, percentage of module completion, and approval ratings. A sample size of 130, α=.05, and power=0.80 will allow for detection of a moderate effect size (*d*=0.50).

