### Randomization and Blinding

Following informed consent, the baseline assessment and confirmation of eligibility, participants will be randomly assigned to 1 of 2 treatment groups: reSET-O or PEAR-008. Randomization lists will be prepared by the study sponsor (Pear Therapeutics) prior to the start of the study. Randomization will be 1:1 and stratified by site and gender with a block size of 10. An electronic list of IDs, access codes, and credentials will be securely provided to the sites. There will be no blinding; this is an open-label study.

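### For retention, the exploratory objective is worded as PEAR-008 against reSET-O, but the Cox model is fitted within each arm and no contrast of the two hazard ratios is planned

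*Protocol article*

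**What the plan says.** The exploratory part of Table 1 gives the objective: "To evaluate the association between engagement with PEAR-008 compared to reSET-O and treatment outcomes (abstinence and retention". Its listed endpoints include use patterns and time to dropout.

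The Exploratory Endpoint Analysis section gives the only engagement-retention analysis, a "Cox proportional hazards model with time to dropout as the dependent variable and the number of active sessions as an independent variable". The next sentence reads: "This analysis will be performed separately for each treatment arm". No treatment term, sessions × arm term or comparison of the two hazard ratios is mentioned.

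Two neighbouring analyses help to place this one. Retention itself is a secondary endpoint, "analyzed using the Kaplan Meier method followed by a log rank test to compare treatment groups". For the other outcome in the same objective, the section says: "The association between abstinence and engagement will be evaluated using a generalized estimating equation model". It does not say how arm enters that model.

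**The concern.** The objective asks a comparative question and the analysis answers two separate ones. Each fit says how sessions relate to dropout within one product. Neither says whether that relation differs between the products, and the section plans no estimate or interval for the difference.

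The question has some substance in this trial. By the article's own description, the two products generate sessions differently. PEAR-008 uses shorter chapters, rewards daily use and repeated chapters, and requires a check-in at the first opening each day. reSET-O prompts for reports every 72 hours. If PEAR-008 produces more sessions, a reader will want to know whether a session carries the same relation to staying in treatment in both arms. This objective is where that would be examined.

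**Working it through.** **1. Objective and method side by side.**

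| Item | Where | Between-arm element |
|---|---|---|
| Engagement-retention objective | Table 1, Exploratory | Yes: PEAR-008 compared with reSET-O |
| Engagement-retention Cox model | Exploratory Endpoint Analysis | None: one fit per arm |
| Time to dropout, log-rank test | Secondary Endpoint Analysis | Yes, but for retention itself, not its link with sessions |
| Active sessions per week, mixed model | Primary Endpoint Analysis | Yes, but for engagement itself |

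No row with a between-arm element estimates how the engagement-retention link differs.

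**2. What the planned fits contain.** The arms are independent. Write b1 and b2 for the two log hazard ratios per unit of sessions, with standard errors SE1 and SE2. Then

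- log ratio of hazard ratios = b1 − b2
- SE of the difference = √(SE1² + SE2²)

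A Cox model with the baseline hazard stratified by arm, and with sessions and sessions × arm as covariates, has a partial likelihood that splits into one factor per arm. It therefore gives the same b1 and b2 as the separate fits, and the interaction coefficient is their difference. The information is already generated; only the contrast is unplanned.

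**3. The plan's own sample size.** "A sample size of 130, α=.05, and power=0.80 will allow for detection of a moderate effect size" (d = 0.50), and "Randomization will be 1:1 and stratified by site and gender with a block size of 10". Taking α as two-sided (the article does not say), a two-sample t test needs 63.8, so 64 per arm or 128 in total, against the stated 130. Power at 65 per arm is 0.81. The figure reproduces. It concerns the primary outcome and says nothing about this analysis.

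**4. Expected precision of the contrast.** Inputs from the article: 130 participants at 1:1, so 65 per arm, followed for 12 weeks. Assumptions: the same dropout proportion in both arms, 20% to 50%; sessions scaled by a common SD, so that the variance of each log hazard ratio is about 1/D, with D the number of dropouts in that arm.

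- SE of the contrast = √(1/D + 1/D) = √(2/D)
- Ratio detectable with 80% power, two-sided 5% = exp[(1.96 + 0.8416) × SE]

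| Assumed dropout | D per arm | SE of contrast | Detectable ratio of hazard ratios |
|---|---|---|---|
| 20% | 13.0 | 0.392 | 3.00 (or 0.33) |
| 30% | 19.5 | 0.320 | 2.45 (or 0.41) |
| 40% | 26.0 | 0.277 | 2.17 (or 0.46) |
| 50% | 32.5 | 0.248 | 2.00 (or 0.50) |

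For the interval, exp(1.96 × 0.392) = 2.16 and exp(1.96 × 0.248) = 1.63. The 95% limits would lie a factor of about 2.2 (20% dropout) to 1.6 (50% dropout) either side of the estimate.

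**The case against.** Four points can be made for the plan.

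- **The comparison is recoverable.** A reader might infer that separate fits make a between-arm comparison impossible. They do not: step 2 shows that the ratio and its interval follow from the two fits. This point stands, and it reduces the defect to a contrast that is not planned.
- **No faulty inference is written down.** A reader might infer that the trial will judge the difference by noting significance in one arm and not in the other. The article does not propose this; for this model it mentions no p value or threshold. One can compute how often two arms with the same true association would disagree on significance, 2p(1−p) for single-arm power p. That is 42% to 50% for p between 0.3 and 0.7, but 18% at p = 0.1 or 0.9. The article gives no p, so the figure does not measure a fault in this plan.
- **The objective is loosely worded.** The comparison with reSET-O recurs in most rows of Table 1, and in this row it attaches to engagement. A within-arm description is a possible reading. The comparative reading is still the natural one, and if the other was meant, the wording should say so.
- **A formal contrast adds little.** It will be imprecise. It also cannot repair other weaknesses: if sessions are totalled over follow-up, early dropouts have fewer by construction, and the article does not say how sessions enter the model. This is a reason to report the ratio modestly, not to omit it.

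It is also tempting to extend the point to abstinence. The article does not say that the abstinence model is fitted by arm, and how arm enters it may properly be left to a fuller document. The point is confined to retention.

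**Conclusion.** The point holds for retention and is minor. The article does not merely leave a detail open: it fixes a by-arm structure with no contrast, under an objective worded as a comparison. The secondary log-rank test does not fill the gap, because it addresses a different quantity.

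Nothing confirmatory depends on it. The primary comparison of sessions and the secondary comparisons of abstinence and retention are unaffected. The mismatch itself rests only on the two places quoted. The precision figures rest on the assumed 20% to 50% dropout, equal dropout and a common SD of sessions in the two arms, and the large-sample variance approximation. Under those assumptions only a two- to threefold ratio of hazard ratios per SD could be detected with 80% power, so a result near 1 would not show that the associations are alike.

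**What to change.** Replace the two separate fits with one Cox model in all randomised participants, containing sessions and sessions × arm, with the baseline hazard stratified by arm. Stratifying avoids adding a proportional-hazards assumption for arm. Use the same unit of sessions in both arms. Report the two arm-specific hazard ratios, which equal those from the planned fits, and their ratio with a 95% confidence interval. Label the ratio an exploratory estimate of low precision, not a decisive test.

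If the sponsor intends only to describe the association within each arm, leave the analysis alone and reword the retention part of the Table 1 objective to say so. Either change brings the two places into agreement.

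The cost is a sentence or two, settled before analysis, with no extra data or participants. The one downside of the added contrast is a wide interval that needs careful wording.
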